#### Time to receipt of recommended services

We assume that 80% in PN arm and 60% in the CCM arm will receive ASD services 5 months after a failed M-CHAT screen. A log rank test will have over 80% power to detect such differences as clinically significant at the 0.05 level.

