**Methods:**

This study uses a hybrid type I randomized effectiveness/implementation design to test effectiveness and collect data on implementation concurrently. It is a two-arm comparative effectiveness trial with a target of 125 participants per arm. Participants are families of children age 15–27 months who receive a positive screen for ASD at a primary care visit at urban clinics in Massachusetts (*n* = 6 clinics), Connecticut (*n* = 1), and Pennsylvania (*n* = 2). The trial measures diagnostic interval (number of days from positive screen to diagnostic determination) and time to receipt of evidence-based ASD services/recommended services (number of days from date of diagnosis to receipt of services) in those with PN compared to and activated control -Conventional Care Management – which is similar to care management received in a high quality medical home. At the same time, a mixed-method implementation evaluation is being carried out.

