### Randomization process

We use stratified, blocked (randomly varying blocks of 2 and 4) randomization to allocate participants to Navigation or CCM. Randomization occurs independently at each primary care recruitment site. Randomization lists are generated in a secure web-based data management system. All outcome assessors are blinded to participant allocation. Written and verbal informed consent is obtained by research staff prior to randomization. Data will be collected in stored in StudyTrax, a commercial clinical research data management tool.

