### Effectiveness outcomes

#### Primary outcomes

The study’s primary outcomes are access to screening, diagnostic, and evidence-based service outcomes (Table 1). The trial measures diagnostic interval (number of days from positive screen to diagnostic determination) and time to receipt of ASD services/recommended services (number of days from date of diagnosis to receipt of services) from review of child’s medical and early intervention records in those with PN compared to CCM.

**Table 1 Tab1:** Diagnostic and Service Outcomes (primary outcomes)

Outcome	Measures	Response	Description
Expedited Evaluation	Achievement of Diagnostic Resolution	Yes/No	Percent children who complete diagnostic assessment within 12-month follow-up
	Timing of Diagnostic Resolution	Timely	Timely- Diagnostic interval ≤ 120 days
		Delayed	Delayed- Diagnostic interval > 120 but ≤ 180 days
		Unresolved	Unresolved - No resolution by 12-months
	Diagnostic Interval	Number of Days	Beginning the day of the positive confirmatory screen and ending the day when family receives determination (yes/no) of ASD diagnosis
Referral to Treatment	Time to receipt of EI services	Number of Days	Days from failed M-CHAT to receipt of services
	Time to receipt of ASD services	Number of Days	Days from Date of diagnosis to ASD services
Engagement in Treatment	Hours of services	Number of Hours	Hours ASD specialty services
	Adequacy of Services	Yes/No	Based on guideline of 25 h/ week
	Absenteeism	Number of absences	Number of family-initiated “no show” and cancellations divided by the number of scheduled appointments in 6 month period following diagnosis
Determination of ASD Diagnosis	ASD diagnosis	Yes/No	Based on ADOS evaluation by Board Certified DBP
Satisfaction with ASD-Services	Client Satisfaction Questionnaire [50]	Categorical and numerical	Previously validated measure of satisfaction with services
	Satisfaction with Hospital Care Questionnaire [50]	Categorical and numerical	Previously validated measure of satisfaction with services
Satisfaction with Navigator	Patient Satisfaction with Interpersonal Relationship with Navigator [51]	Categorical and numerical	Newly validated 9-item scale to assess satisfaction with the interpersonal relationship with navigators

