### Sample size and power

According to Kraemer’s threshold of clinical significance concept [38], we estimate a required sample size of 250 to detect the smallest differences in primary outcomes that are of clinical importance. In the ITT analysis, we assess the adequacy of the expected sample to detect main effects among all children randomized, assuming a two-sided alpha of 0.05. We present power calculations for planned categorical analyses. Power to detect between group differences in analyses of count data will exceed those presented below.

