#### Completion of diagnostic evaluation

In our pilot work, 50% of children who are referred for developmental evaluations complete the evaluation. We aim for a 90% completion rate, which is consistent with our pilot PN study data and assume a marginal improvement in the CCM arm to 65%. With the expected sample, we will have > 90% power to detect clinically significant differences by treatment arm in ITT and explanatory analyses.

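### The power above 80% for time to services is calculated on a different time origin and population from the primary outcome it is meant to support

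*Protocol article*

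**What the plan says.** All references are to the protocol article.

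- **Outcome.** The Abstract (Methods) and Primary outcomes sections run the second primary outcome from the date of diagnosis to receipt of services. The Table 1 row for ASD services says "Days from Date of diagnosis to ASD services". Table 1 also has a services row timed from the failed M-CHAT, but for EI services.
- **Power for that outcome.** The subsection headed Time to receipt of recommended services states: "We assume that 80% in PN arm and 60% in the CCM arm will receive ASD services 5 months after a failed M-CHAT screen". The power claimed for the log-rank test is above 80%.
- **Frame for power.** Under Sample size and power, "we estimate a required sample size of 250", with main effects assessed in all children randomized, "assuming a two-sided alpha of 0.05". The Abstract gives the trial "with a target of 125 participants per arm". Intervention main effects also puts every randomized child in the denominator.
- **Diagnostic completion.** The target for PN is 90%. For CCM the authors "assume a marginal improvement in the CCM arm to 65" per cent. That section gives no horizon; Table 1 defines the completion measure as "Percent children who complete diagnostic assessment within 12-month follow-up".
- **ASD status.** Table 1 allows the diagnostic determination to be yes or no. No expected share of ASD-positive children is given.

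**The concern.** The power sentence and the outcome definition differ in two ways. The first is the clock: the failed screen in one, the diagnosis in the other. The second is the population: a screen-based clock starts for every randomized child, while a diagnosis-based clock starts only for children who reach a diagnosis, and the plan expects that fraction to differ by arm. A PN advantage measured from the screen can come entirely from more or faster diagnosis, which is the first primary outcome. It says nothing by itself about the interval after diagnosis, which is the second.

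At stake is how a null result on time to services would be read. Without a power figure for the declared outcome, nobody can say whether such a result is informative or merely imprecise.

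**Working it through.** **Inputs.** 125 per arm (Abstract), with 1:1 allocation consistent with "stratified, blocked (randomly varying blocks of 2 and 4) randomization". Two-sided alpha 0.05. Service rates 80% v 60% at 5 months. Completion 90% v 65%. Let *f* be the share of completers diagnosed with ASD. It is not stated, so it is varied and taken as equal in the two arms.

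**1. Reproduce the stated figure.** Under proportional hazards:

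- HR = ln(1 − 0.80)/ln(1 − 0.60) = 1.756, so ln HR = 0.563.
- Events = 125 × 0.80 + 125 × 0.60 = 175.
- Schoenfeld power = Φ(√(175 × 0.25) × 0.563 − 1.96) = Φ(1.77) = 96%.

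Freedman's formula gives 95%, a two-proportion test 94% and a simulated log-rank test (4,000 runs, censored at 5 months) 96%. About 99 events are enough for 80% power (Schoenfeld). The claim of more than 80% is correct for these inputs.

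**2. Read 80%/60% as rates in all randomized children.** If ASD services follow a completed evaluation, the implied rates among completers are:

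- PN: 0.80/0.90 = 88.9%.
- CCM: 0.60/0.65 = 92.3%.

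These shares of completers would have to be evaluated, found to have ASD and in services within 5 months of the screen. Yet Table 1 counts completion over 12 months and has a delayed category for intervals above 120 and up to 180 days, so some completers would be diagnosed after month 5.

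The PN rate is the lower of the two. The crude hazard ratio among completers is ln(1 − 0.889)/ln(1 − 0.923) = 0.86, slightly in favour of CCM. On this reading the assumption contains no PN benefit on the diagnosis-to-services interval.

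**3. Read 80%/60% as rates among diagnosed children.** The numbers available are 125 × 0.90 × *f* = 112.5*f* (PN) and 125 × 0.65 × *f* = 81.25*f* (CCM), a PN share of 0.581. Events = (112.5 × 0.80 + 81.25 × 0.60)*f* = 138.75*f*. Schoenfeld power = Φ(√(138.75*f* × 0.581 × 0.419) × 0.563 − 1.96). The simulated columns assume constant hazards.

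| ASD share *f* | Schoenfeld, 5 months | Two proportions | Simulated log-rank, 5 months | Simulated log-rank, 12 months |
|---|---|---|---|---|
| 1.0 | 91% | 86% | 89% | 96% |
| 0.8 | 83% | 78% | 82% | 92% |
| 0.7 | 78% | 72% | 77% | 87% |
| 0.6 | 72% | 65% | 70% | 83% |
| 0.5 | 64% | 58% | 62% | 75% |

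Schoenfeld power falls below 80% when *f* is under about 0.73; for the two-proportion test the threshold is about 0.85. With 12 months of follow-up, simulated power is still 83% at *f* = 0.6.

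**4. Take the product over all randomized children.** If 80%/60% are rates among the diagnosed but every randomized child is in the denominator, then at *f* = 0.5 the rates are 0.90 × 0.5 × 0.80 = 36% v 0.65 × 0.5 × 0.60 = 19.5%. Then HR = ln(0.64)/ln(0.805) = 2.06, events = 125 × (0.36 + 0.195) = 69.4, and power is 85%. So the same assumptions give 64% or 85% at *f* = 0.5, depending only on the denominator.

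**The case against.** The strongest reply is that nothing is miscalculated and no shortfall is shown. Most of this stands.

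- The stated power is reproduced with room to spare.
- A reader might infer that 80%/60% contradicts 90%/65%. It does not strictly: 80 is below 90, 60 is below 65, and the rates required among completers are demanding but possible.
- A reader might infer that the trial is underpowered for services. The documents do not support that. Restricting to completers alone still gives 86–91%. Every figure below 80% needs an ASD share that the article does not state and that the full protocol may contain. Censoring at 5 months is also an assumption, since the text gives rates at that time without saying follow-up stops there.
- The outcome is worded as ASD or recommended services, so children found not to have ASD may be able to have an event. The power sentence itself says ASD services, so this is an ambiguity to settle.
- A screen-based clock fits the all-randomized denominator better than a diagnosis-based one does. That is a fair argument for changing the outcome's time origin, but it concedes that the two do not match at present.

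The reply does not remove the mismatch. Both time origins are written into the article, and the only power figure for this outcome uses the one that the outcome definition does not.

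**Conclusion.** The point holds as a mismatch of time origin and population, not as an arithmetic error or a demonstrated lack of power. The stated figure is correct for receipt of ASD services by 5 months from the screen in 125 per arm (94–96%). It does not describe power for days from diagnosis to services.

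How much this matters depends on the reading. Over all randomized children, the assumed rates carry no PN effect after diagnosis (crude hazard ratio about 0.86, assuming services follow evaluation and the ASD share is equal by arm). Among diagnosed children, Schoenfeld power with 5-month censoring runs from 91% down to 64% as the ASD share goes from 1.0 to 0.5, crossing 80% at about 0.73, or at a lower share with longer follow-up. That range is conditional on an unstated share.

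**What to change.** 1. Choose one time origin and one denominator for time to services, and use them in Primary outcomes and Table 1, in Intervention main effects and in the power section. If the clock starts at diagnosis, say how randomized children without a diagnosis date enter the analysis.
2. State whether recommended services received by children found not to have ASD count as events.
3. Restate the power for the outcome so defined, built from the 90%/65% completion, a range of ASD shares and the share of diagnosed children served by the stated time. Give the follow-up assumed.

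The cost is rewording and a short recalculation, with no increase in enrolment. The restated power may turn out lower or higher than 80%, depending on the definition chosen.

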### Data and safety monitoring board (DSMB)

Our data and safety monitoring board, consisting of autism intervention experts, will meet quarterly to review study procedures. Any adverse events will be reported immediately to both the IRB and DSMB.

### Implementation evaluation

Our evaluation of PN implementation will be done prospectively using a mixed methods approach. Three aims will be carried out sequentially, with each project informing the next. Data will also be triangulated in the final analysis. In aim 1, using a Failure Modes and Effects Analysis, we will lead a team of stakeholders in mapping the navigator intervention to identify and analyze failures in implementation. In aim 2, we will use semi-structured interviews, based on the failures identified in aim 1 and CFIR, to assess barriers and facilitators to implementing navigation. In aim 3, we will use multilevel statistical modeling to examine parent, providers, organizational, and state-level factors that predict implementation success. Success will be defined as fidelity to the intervention, which will be defined as completion of each of the 32 components of the navigation model (e.g. initial family contact, sending introductory letter to PCP, assisting in paperwork for DBP intake visit, completing social security insurance application).

### Process mapping and analysis

Using a Failure Modes and Effects Analysis (FMEA), we will lead a team of stakeholders in mapping navigation to identify and analyze failures in implementation. FMEA is a systematic method for evaluating where intervention processes can fail, and assessing the relative impact of different failures [39]. FMEA follows a proscribed methodology involving process mapping and evaluating failure modes, causes, and consequences. Originally used in engineering fields, FMEA is used regularly in healthcare settings [39], and is particularly useful in evaluating processes – like PN– *prior* to real-world implementation.

We will assemble three multidisciplinary teams that uniquely reflect PN processes in each of the study venues. Participants will include primary care pediatricians, social workers, navigators, nurses, project coordinators, clinic directors, an expert in PN, and an expert in ASD services for minority children. Through a series of face-to-face and videoconference meetings, these multidisciplinary teams will map the process of PN – focusing specifically on screening and identifying participants; engaging participants with their navigators; and delivering navigation with appropriate safety and fidelity.

For each step in the process map, teams will list all possible failure modes (i.e. anything that has gone, or could go, wrong in implementing the step), along with the causes and consequences of that failure. For example, in delivering PN with proper fidelity, a process failure could occur if an insufficient number of sessions are delivered, or if the patient navigator practices the technique incorrectly. Whereas the former – insufficient number of sessions delivered - might be caused by a mismatch in schedules between navigator and parent, the latter – incorrect technique - might be caused by insufficient navigator training or supervision.

#### Risk priority calculation

For each failure mode, we will calculate a risk priority number – a composite score that reflects three fundamental dimensions of an actual or latent failure and the risk that it poses to program implementation: likelihood of ocurrence, likelihood of detection, and severity. Each team will assign a numeric value between 1 and 10 to each dimension; the risk priority number is the product of the three and thus ranges between 1 and 1000. Failure modes with the highest risk priority numbers represent significant threats to implementation and will be probed in depth among participants (aim 2).

#### Comparative analysis across settings

We will compare each of the above indices across study venues – noting similarities and differences of all actual and potential failures. We will compare the acceptability of navigation to families in each venue and determine whether differences in fidelity exist by delivery system*.*

### Qualitative interviews

We will employ CFIR [24] to conduct a series of semi-structured interviews with key stakeholders to evaluate barriers and facilitators to delivering PN. The purpose of these interviews is to better understand the high risk failure modes identified in our process mapping. The component domains of CFIR will guide the interview protocol (Intervention Characteristics, Outer setting, Inner setting, Characteristics of Individuals, Process). Participants will be grouped into the following categories: a) physicians (*n* = 30), clinic administrators and directors (*n* = 8) and policy experts (*n* = 6); b) navigators (n = 8); and c) parents of children with ASD (*n* = 45). We will probe answers to understand how each CFIR construct relates to their experience. Our questions will focus on understanding both the individual perspective and the contextual impact.

We will use content analysis and a deductive approach. We will use the CFIR coding framework (available at www.cfirguide.org/) [32] to code our data, but will also be open to new themes that may emerge. Our coding process will be guided by consensual qualitative methods. Multiple coders will be used throughout data analysis process to foster various perspectives and validation will be carried out through deliberation and consensus. A summary memo will be developed for each category of interviewee using a two-level deliberated consensus approach. First, two investigators will independently code an individual transcript. Then, they will meet and compare coding and agreed on final codes. Finally, they will write a case memo, organized by CFIR construct with summary statements and supporting quotes. Investigators will refine the memo as they continue analysis, until all transcripts are coded, using each new transcript to confirm previous summary statements or add new information. The study team will meet weekly to review memos.

Each memo will be rated using a consensus process to assign a rating to each construct within each category of interviewee (parent, provider, navigator, policy expert). Ratings will reflect the direction of influence (positive or negative) and the magnitude of each construct. Once all constructs for all cases are rated, we will compare ratings for each construct across categories. This approach combines the strengths of a case-oriented method, which allows for rich context-specific consideration when rating each construct, with a variable-oriented method, which promotes identifying patterns and relationships by construct across cases to heighten overall validity of ratings.

### Multilevel model

We will use multilevel statistical modeling to examine parent, navigator, organizational, and state policy factors that predict implementation success (Table 2). Success will be defined as fidelity to the intervention model. Navigator fidelity will be the primary outcome as it a critical component of implementing any intervention, and the most commonly measured implementation metric [32]. We will measure fidelity at the completion of the navigator protocol. Fidelity will be defined as: 1) completion of the three home visits; 2) completion of Navigator log; and 3) adherence to the eight constructs of motivational interviewing expected to be performed by the navigators.

**Table 2 Tab2:** Measures for Multi-level Model of Navigator Fidelity

Measure	Tools	Level
Provider Density	Publically available data on certified ASD providers	State
Diagnostic Availability	Publically available data on number of ASD diagnostic centers	State
Characteristics	Organization location, size, and type	Organizational
Organizational Readiness to Change	Organizational Readiness to Change Assessment tool [52]	Organizational
Demographics	Age, race, ethnicity, gender, education, language proficiency	Navigator
Experience with ASD	Question developed by study team	Navigator
Cultural competency	Dogra’s Cultural Awareness Questionnaire [53]	Navigator
Navigator proficiency	Measure developed from Navigator training manual	Navigator
Demographics	Age, race, ethnicity, child’s gender, comorbid conditions, parental education, nativity, English proficiency, access to transportation, insurance	Parent
Parental social support	MOS-Social Support Survey [54]	Parent
Global perceived stress	Perceived Stress Scale- Self Report 14 item [55]	Parent
Parenting stress	Parenting Stress Index 4th edition – Short Form [56]	Parent
Physical/emotional health	Veterans RAND 12 Item Health Survey [57]	Parent
Parental coping strategies	Brief COPE [58]	Parent
Child’s impact on the family	Family Impact Questionnaire [59]	Parent
Parenting stress from ASD	Autism Parenting Stress Index [60]	Parent
Parental perceived mastery	Pearlin Mastery Scale [61]	Parent
Child’s adaptive functioning	Adaptive Behavior Assessment System II [62]	Parent

We will combine three data sets: parent-reported measures collected at three time points throughout the study; primary surveys of navigator and clinic data collected in year one (clinic) and three (navigator) of the project; and publically available state-level data.

First, we will evaluate bivariate associations between parent, navigator, organizational, and state-level predictors and navigation model fidelity using χ2 test for pairs of categorical variables and 1-way ANOVA for comparing continuous and categorical variables. Since the data has a 4-level structure, with many individual families nested within navigators, navigators nested within organizations, and organizations nested within states, multilevel logistic regression will be used to account for the lack of independence. We will calculate the intraclass correlation in a null model to analyze how much of the variance in our outcome can be potentially attributed to the predictor level. This will be followed by a series of models: model #1 will examine the unadjusted association between state resources and outcomes, model #2 will add organizational characteristics to model #1; model #3 will add to model #2 by adjusting for navigator level characteristics; model #4 will further adjust model #3 for parent characteristics, and finally, model #5 will add to model #4 by adjusting for parent-reported measures.

In our sample of three states, we propose to evaluate data from 12 clinics, 8 patient navigators and 125 parents. To account for the clustered design, our estimation of power was adjusted via a design effect using an estimate of within subject correlation of the outcome parameter. A proportion of non-fidelity at the mean of 20% compared to a proportion of 0.10 at 1 SD above the mean for the predictor will yield an odds ratio of 0.44. Assuming the design effect will be no larger than 1.41 (the square root of 2), the statistical power should be computed based on a sample size of 89 for an observed sample of 125 parents. For 89 parents, the above-noted difference with an odds ratio of 0.44 will have 82% power with a two-sided alpha of 0.05.

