### Intervention

PN is a theory-based, empirically-supported, multicomponent, manualized care management strategy [26, 27]. It differs from other care management strategies in that it focuses on overcoming patient-specific barriers to a defined set of services over a defined, time-limited period. PN is well established in cancer care as a means to reduce disparities in the critical interval between a positive screening test (for example, a mammogram for breast cancer) and definitive diagnosis [16, 17, 28], decrease anxiety [29], and increase satisfaction with services [29]. The goal of PN is to integrate a disjointed health care system on behalf of an individual patient. In our proposal, we build upon the established principles of PN but expand the navigator role in novel ways. Navigation services are provided to the family unit by bilingual paraprofessionals. It is extended to integrate a fragmented network of ASD services that requires coordination among community-based and educational services, as well as those provided by the conventional health care team.

Additionally, PN is augmented with evidence-based behavior change strategies – motivational interviewing and collaborative decision making – that support patient engagement and self-management skills. A typical PN activity may be to assist a parent with marginal literacy to complete a clinic’s patient questionnaires, help a family know what to expect during a stressful ASD diagnostic evaluation, or coordinate childcare around a child’s early intervention schedule. In this proposal, the systemic PN protocol begins after referral for an autism evaluation and end 100 days after diagnostic resolution – at which time, a child with ASD would be expected to be engaged and retained in intensive early intervention services (based on the guidance from Autism Speaks) [30]. Navigators follow a standardized protocol, keep extensive structured logs of their work, and a random subset of encounters are audio recorded. Data are captured on all interactions with families, providers, medical, educational, and social service organizations, recording time spent, activities performed, and barriers addressed.

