### Secondary outcomes

A number of secondary outcomes such as number of children diagnosed with ASD, satisfaction with the navigator, and an array of parent-reported measures (e.g. parenting stress, social support, and coping responses) and are assessed (see Table 1 for full list of measures) at the time of entry into the study, as well as at three follow-up time points. Additional process outcomes will include confirmatory screening results, referrals to care, and service use and are obtained from care manager and navigator logs and from the child’s medical, early intervention, and ASD service provider records.

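### Navigator predictors of fidelity are surveyed in project year three, while fidelity is scored as each family finishes; for families who finish earlier, predictors that practice can change are measured after the outcome

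*Protocol article*

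**What the plan says.** The Multilevel model section of the protocol article sets out to "examine parent, navigator, organizational, and state policy factors that predict implementation success". Success means navigator fidelity. Table 2 lists four navigator-level predictors: demographics, experience with ASD, cultural competency, and proficiency (a measure built from the training manual). They enter the model sequence at the third step: "model #3 will add to model #2 by adjusting for navigator level characteristics". They stay in models 4 and 5.

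On timing, the same section names "primary surveys of navigator and clinic data collected in year one (clinic) and three (navigator) of the project". For the outcome it says: "We will measure fidelity at the completion of the navigator protocol". The Intervention section fixes when that is for a family, because navigation "begins after referral for an autism evaluation and end 100 days after diagnostic resolution".

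The planned data come from 12 clinics, 8 navigators and 125 parents.

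**The concern.** A predictor should be measured before the outcome, or be something the outcome cannot alter. Here the clinic survey comes early, but the only stated navigator survey comes late, while the outcome builds up family by family from the first completed protocol onward.

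This matters most for attributes that practice can change. A navigator who has carried many families through the protocol may score higher on proficiency or cultural competency because of that work. ASD experience may behave in the same way, depending on how the question is worded. If so, part of a positive association with fidelity reflects delivery raising the score, not the score predicting delivery. Each of the 8 navigators' scores is shared by about 125/8 = 15.6 families, so one score that has moved with practice affects many rows of the data.

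The article intends these results to inform dissemination of navigation. A misdirected association could mislead choices about which navigators to recruit or what to train.

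**Working it through.** The plan states no figure for this point, so there is none to reproduce. The order of measurement follows from the text. Arithmetic only indicates how many families could be affected.

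**Inputs from the article**
- Navigator survey: project year three, point within the year not given.
- Fidelity: scored at the end of the navigator protocol, 100 days after diagnostic resolution.
- Diagnostic interval: Table 1 uses cut-offs of 120 days, 180 days and 12 months. The last is the horizon for "Percent children who complete diagnostic assessment within 12-month follow-up".
- Navigation families: 125.

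**Step 1. Order of measurement.** A family whose protocol ends before the survey has its outcome fixed before the navigator predictor is recorded. A family whose protocol ends after the survey does not have this problem.

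**Step 2. Length of the navigator protocol per family**, counted approximately from the screen: L = days to resolution + 100.
- 120 + 100 = 220 days (0.60 years)
- 180 + 100 = 280 days (0.77 years)
- 365 + 100 = 465 days (1.27 years)

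**Step 3. Share of families already scored at project time T.** With even enrolment from t0 to t1 (in years), the share is (T − L − t0)/(t1 − t0), limited to the range 0 to 1. The enrolment dates are assumptions, because the article gives none.

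With t0 = 0 and t1 = 3:

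| L | Start of year three (T = 2) | End of year three (T = 3) |
|---|---|---|
| 220 days | (2 − 0.60)/3 = 47%, 58 families | (3 − 0.60)/3 = 80%, 100 families |
| 280 days | (2 − 0.77)/3 = 41%, 51 families | (3 − 0.77)/3 = 74%, 93 families |
| 465 days | (2 − 1.27)/3 = 24%, 30 families | (3 − 1.27)/3 = 58%, 72 families |

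**Step 4. Sensitivity to the dates.** With enrolment starting at year 0, 0.5 or 1 and ending at year 2, 3 or 4, and the same three lengths:
- Start of year three: 0% to 70%
- Middle of year three: 8% to 95%
- End of year three: 24% to 100%

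The share reaches 100% only when enrolment ends by year 2, resolution takes at most 180 days, and the survey falls at the very end of year three.

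**Step 5. Which predictors are exposed.** Age, race, ethnicity and gender are fixed or recoverable, so late collection does them little harm. Proficiency and cultural competency can move with practice. ASD experience may or may not, because the question's wording is not shown.

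**The case against.** The strongest reply is that the article gives no project length, no enrolment dates and no point within year three, so the overlap between survey and outcome cannot be established. That stands as to size: the share could be small. It does not remove the point, because the article positively states a late navigator survey and an outcome scored family by family, and nothing in it restricts the model to families who finish after the survey.

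A second reply is that this is a formative, secondary analysis, and that 8 navigators support only weak navigator-level inference whatever the survey date. That also stands, and it limits how much the change can gain. It is no reason to keep an avoidable ordering problem.

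A reader might infer more than the documents support:
- **That all families are scored before the survey.** The missing calendar rules out that claim. Nor is it right to take the families entering before year three (2/3 × 125 = 83 under even three-year enrolment) as the number affected. Entry is not scoring, and navigation runs for months after entry.
- **That navigators who leave before year three have no data and their families drop out of models 3 to 5.** The article mentions no turnover, does not say leavers go unsurveyed, and does not state a complete-case analysis. It lists 8 navigators both for interview and for the model, so it expects data from all of them.
- **That the parent-reported predictors share the fault.** The Multilevel model section speaks of "parent-reported measures collected at three time points throughout the study", and the Secondary outcomes section of measurement "at the time of entry into the study, as well as at three follow-up time points". An entry value therefore exists. Which time point enters model 5 is a detail that an article may leave to the full plan.

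**Conclusion.** The point holds in limited form. As stated, the timing lets navigator proficiency, cultural competency and possibly ASD experience be measured after the fidelity they are meant to predict, for every family who finishes before the year-three survey. For those families the direction of an association in models 3 to 5 cannot be read from the data.

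The number of such families is unknown. The 30 to 58 families at the start of year three, and 72 to 100 at its end, rest on even enrolment over exactly three project years and on resolution between 120 days and 12 months. The other assumed dates span 0% to 100%, so no single figure should be quoted as the size of the problem.

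The consequence is confined to the navigator-level part of aim 3. The randomized comparison of navigation with conventional care management is untouched. This is an inexpensive improvement to a secondary analysis, not a threat to the trial's main conclusions.

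**What to change.** Give the navigator survey after each navigator's training and before that navigator's first family, and state in the Multilevel model section that these values are the navigator predictors in models 3 to 5. Keep the year-three survey only to describe change over the project.

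If navigators have already started, use only fixed or at-hire items (for example demographics, and ASD experience asked as of hire) as predictors for families already completed.

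The cost is one earlier survey of 8 people and a sentence in the model description. The downside is that no year-three proficiency value is available as a predictor.
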